**Fig 2 pone.0310178.g002:**
[figure not shown]
SPIRIT schedule of enrolment, interventions, and assessments of the study. The outcomes include the number and percentage of participating sessions, the duration and percentage of participating sessions during self-exercises, the number and percentage of successful sessions, the mean amplitude of muscle contractions in a session, the number and percentage of completed conventional physiotherapy sessions, the duration and percentage of conventional physiotherapy sessions, and the assessment results for RMA, MMT, BRS, mRS, FMS-LE, FAC, BBS, and SF-36 version 2.0. PRPS: Pittsburgh Rehabilitation Participation Scale; RMA: Revised Motor Assessment; MMT: Manual Muscle Test; BRS: Brunnstrom Recovery Stage; mRS: Modified Rankin Scale; FMS-LE: Fugl–Meyer Assessment of the Lower Extremity; FAC: Functional Ambulation Category; BBS: Berg Balance Scale; SF-36: 36-item Short-Form Survey.

### 2.4. Interventions

#### 2.4.1 Conventional rehabilitation

The conventional stroke rehabilitation program involves a comprehensive and individualized approach that includes range of motion exercises, strengthening exercises, balance and coordination exercises, and exercises for functional mobility such as sitting balance, sit-up, sit-to-stand, standing, and gait [25]. The amount and intensity of the conventional rehabilitation program are equally provided for participants of both intervention and control groups by the same group of physical therapists who are blinded to the group allocation. Physical therapists will provide conventional rehabilitation for 30 minutes each session, two sessions a day, five times a week, in both groups. Patients with stroke may receive physical therapy with walking aids, such as a walker or cane, or a lower-extremity orthosis.

#### 2.4.2 In-bed self-exercises based on EMG-sensor feedback system

In-bed self-exercises based on EMG-sensor feedback are conducted using wireless EMG sensors (HSN2ER3E, SMD Solution, Seoul, Republic of Korea) and mobile applications (HSN2ER3E S/W, Myoverse, SMD Solution, Seoul, Republic of Korea) in Fig 3.

**Fig 3 pone.0310178.g003:**
[figure not shown]
Images of electromyography sensor and sensor patch. (A) An electromyography sensor; (B) electromyography sensor patch; (C) the attachment of EMG sensors to the lower extremities using sensor patches.

Two versions of mobile applications are provided for therapists and patients with stroke, respectively, because the contents of information provided for therapists and patients with stroke are different. Fig 4 shows the visualized results of EMG-sensor feedback in the mobile applications for patients with stroke: (A) the type, posture, dose, and instructions of prescribed exercises; (B) a message for participants to contract the target muscles; (C) ongoing exercise performances, including repetitions per set, sessions per day, and sets per session; (D) the bar graph representing the percentage of the peak EMG signals relative to their target amplitude during muscle contractions; (E) buttons for pause and termination of prescribed exercises. The mobile applications for therapists have the following features, including the EMG values of the targeted muscles during self-exercises and the prescription contents of the exercise period, the session, sets, and repetitions for the selected self-exercises, which can be monitored by physical therapists to identify ongoing exercise performances (Fig 5). If the usage frequency of the mobile application is low or the recorded levels of EMG signals are lower than expected, the physical therapists will contact the patients to check their conditions or investigate the reasons for the low performance. Based on the developed an in-bed self-exercise protocol, the exercise program will be adjusted weekly according to the muscle strength and Brunnstrom recovery stage by therapists. Additionally, the exercise regimen is reassessed and prescribed anew each week, with the amplitude of EMG signals during MVC being reassessed each time.

**Fig 4 pone.0310178.g004:**
[figure not shown]
The visualized results of EMG-sensor feedback in the mobile applications for patients with stroke. (A) The type, posture, dose, and instructions of prescribed exercises; (B) a message for participants to contract the target muscles; (C) ongoing exercise performances, including repetitions per set, sessions per day, and sets per session; (D) the bar graph representing the percentage of the peak EMG signals relative to their target amplitude during muscle contractions; (E) buttons for pause and termination of prescribed exercises.

**Fig 5 pone.0310178.g005:**
[figure not shown]
The visualized results of EMG-sensor feedback in the mobile applications for therapists. (A) Visualization of performance history with a Bar Graph; (B) the results of the self-exercises including session frequency and duration, number of sets and repetitions, rest intervals, exercise type, intensity level, and progression.

The participants will be instructed to complete at least two 30-minute sessions per day, 5 days a week, for a duration of 3 weeks of in-bed self-exercises, in addition to their conventional rehabilitation sessions. The participants will be provided with information including the type, dosage (e.g., repetitions, sets, and sessions), duration, intensity (% of EMG activities during maximal voluntary contractions), and body positions of lower-limb exercises, along with real-time feedback on their muscular activities and goal achievement. EMG signals will be measured and collected weekly during the intervention period, and the prescription contents of the self-exercises will be changed considering the results of goal achievement and the levels of Brunnstrom recovery stage (BRS) and muscle strength (Fig 6). Additionally, the exercise information of the participants, including goal achievement, exercise frequency, and exercise duration, will be monitored daily through a mobile applications for therapist. The therapists will provide participants with personal support and education to motivate them and address any barriers to their commitment.

**Fig 6 pone.0310178.g006:**
[figure not shown]
Protocol to determine the level and step based on the Brunnstrom recovery stage and muscle strength.

The setting levels of the surface EMG activities at the target muscles are as follows. To acquire EMG signals from the vastus lateralis and tibialis anterior, surface electrodes will be positioned over the muscle bellies along a line parallel to the orientation of the muscle fibers and attached to the skin using a specialized patch. The surface electrode sites will be located at the following positions: (1) at the halfway position on the line from the anterior spina iliac superior to the lateral side of the patella for the vastus lateralis and (2) at the one-third position on the line from the fibular head to the medial malleolus for the tibialis anterior [26, 27]. Surface EMG electrodes will be attached by patients with stroke or caregivers at predetermined locations on the vastus lateralis and tibialis anterior muscles, which will be marked by the therapists. The posture of the self-exercises to activate the lower-limb muscles will be determined and instructed before maximal voluntary contractions. This study adopted the target level of EMG activities for patients with subacute stroke when engaging in self-exercises as 50% of the mean activities during three trials of the maximal voluntary contractions (MVC) according to a previous systematic review [28].

The principles for determining the level and step of in-bed self-exercises in stroke patients are presented in Figs 6–8. There are three levels according to the BRS, and each level has three steps according to the Medical Research Council scale for muscle strength. The specific principles are as follows: (A) The level and step are determined based on the BRS and muscle strength, and self-exercises are prescribed by physiatrists or physical therapists accordingly. (B) The level or step and exercises prescription can be changed based on the BRS and muscle strength by physiatrists or physical therapists every week. (C) Up to four types of self-exercises can be selected during a 1-week period, and exercises corresponding to the highest level or step are recommended by physiatrists or physical therapists considering the patient’s condition. (D) The level or step may overlap, and exercises corresponding to the highest level are recommended based on the patient’s condition. (E) The physiatrists or physical therapists determine postures that patients can perform safely and effectively during exercises. If possible, postures with high functional mobility are recommended. Caregivers can help participants to adjust and maintain postures during in-bed self-exercises, if necessary. (F) Information on the types of exercises, sessions per day, sets per session, repetitions per set, and target amplitude of the EMG signals during exercises will be provided to the patients. In general, self-exercises will be recommended at 2 types of self-exercises per session, 2–3 sessions per day, 3–5 sets per session, and 5–10 repetitions per set, with an amplitude of at least 50% of the amplitude of EMG signals during maximal muscle contraction. This will be determined by physiatrists or physical therapists based on the patient’s degree of exercises performance. (G) It is recommended to initially perform truncal balance exercises for 10 minutes as a warm-up to ensure safety before initiating sessions of in-bed self-exercises. Truncal balance exercises may include pelvic tilts, seated or standing trunk rotations, leg lifts while maintaining a stable trunk, bridging, and reaching tasks while seated or standing. Truncal balance exercises are also considered as a part of the conventional rehabilitation program in both groups. Thus, truncal balance exercises will be provided for participants in both intervention and control groups as conventional rehabilitation if necessary. (H) It is recommended that two or fewer EMG sensors are used during self-exercises and attached to the sites of paralyzed muscles, where the physiatrists or physical therapists indicate.

**Fig 7 pone.0310178.g007:**
[figure not shown]
Contents of self-exercises based on the levels and steps in patients with subacute stroke.

**Fig 8 pone.0310178.g008:**
[figure not shown]
Contents of self-exercises based on postures in patients with subacute stroke.

### 2.5. Outcome measures

#### 2.5.1. Primary and secondary outcome measures

The baseline clinical characteristics will be collected as follows: age, sex, dominant hand, presence or absence of other diseases (high blood pressure, diabetes, hyperlipidemia, atrial fibrillation, Charlson comorbidity index), level of education; caregiver (spouse, children, others), National Institutes of Health Stroke Scale score, stroke treatment (thrombolysis/thrombectomy), stroke onset (day), lesion type (infarction, hemorrhage), lesion location (supra-tentorial, infra-tentorial), lesion laterality (right, left), stroke causes (TOAST classification: large-artery atherosclerosis/small-vessel occlusion/cardioembolic/other determined etiology/undetermined etiology), medicines for depression, spasticity, and epilepsy, Mini-Mental State Examination score, motor-evoked potential, Hospital Anxiety and Depression Scale score, and orthosis.

The primary outcome measure is the Pittsburgh Rehabilitation Participation Scale (PRPS). The PRPS is a clinician-administered instrument designed to assess the participation of patients in rehabilitation [29, 30]. It is rated on a scale of 1–6 to measure a patient’s effort and activity to participate in rehabilitation. The patient’s session participation and effort levels were assessed across six distinct categories, ranging from "none" to "excellent." The "none" category signifies that the patient either declined to participate in the entire session or did not engage in any exercises during the session. Conversely, the "excellent" category denotes that the patient actively participated in all exercises with maximal effort, successfully completing each exercise and displaying a keen interest in both the exercises and any future therapy sessions. The remaining categories describe varying degrees of participation and effort between these two extremes [30]. In the PRPS, there are three types of exercise sessions to be newly defined as follows: (i) a participating session, in which the number of contractions of target muscles is more than one; (ii) an effortful session, in which the amplitude of one or more target muscles during contractions is more than 20% of maximal voluntary isometric contraction; (iii) a successful session, a session in which the amplitude of one or more target muscles during contractions is more than 50% of maximal voluntary isometric contraction. The six categories of PRPS using the concept of participating, effortful, and successful sessions are defined as follows: (i) none, 0% of participating sessions; (ii) poor, <50% of participating sessions; (iii) fair, ≥50% of participating sessions and <50% of effortful sessions; (iv) good, ≥90% of participating sessions, ≥50% and <90% of effortful sessions; (v) very good, ≥90% of participating sessions, ≥90% of effortful sessions, and ≥90% of successful sessions; (vi) excellent, ≥90% of participating sessions, ≥90% of effortful sessions, ≥90% of successful sessions, and active involvement in establishing exercise plans for future sessions (Fig 9).

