Self-exercises under intermittent supervision by physical therapists could serve as an alternative to efficiently augment the training volume for hospitalized stroke patients [16, 17]. Self-exercises are a crucial component of strategies such as telerehabilitation and self-administration to increase the dose of rehabilitation training [18, 19]. A recent systematic review showed that the effect of self-exercises on post-stroke motor function was equivalent to that of conventional rehabilitation [20]. However, although self-exercises can help compensate for the shortage of training during hospitalization [21, 22], its inherent limitations, such as its repetitive nature and lack of feedback, may restrict its effectiveness in improving motor recovery [23, 24].

Wearable electromyography (EMG) sensors can be utilized to acquire data on muscular activity, potentially enabling monitoring of the quantity and quality of self-exercises and tailoring rehabilitation programs for individual patients by adjusting the grades of self-exercises. This study aims to investigate the feasibility and safety of in-bed self-exercises based on EMG sensor feedback in patients with subacute stroke. Towards this goal, we developed a novel self-exercise protocol incorporating wearable EMG sensors to provide biofeedback to stroke patients. In this study, we hypothesize that there will be a statistically significant difference in Pittsburgh Rehabilitation Participation Scales among subacute stroke patients who receive conventional lower extremity rehabilitation compared to those who receive rehabilitation based on feedback using data obtained via electromyography-supervised self-exercise. Specifically, the null hypothesis (H₀) posits no significant difference between the two groups, while the alternative hypothesis (H₁) posits a significant difference in the participation scales.

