**Fig 9 pone.0310178.g009:**
[figure not shown]
Pittsburgh Rehabilitation Participation Scale and newly defined exercise sessions.

The secondary outcome measures are the number and percentage of participating sessions, the number and percentage of effortful sessions, the number and percentage of successful sessions, the mean amplitude of muscle contractions in a session, and the duration and percentage of participating sessions during self-exercises. Rivermead Motor Assessment, Manual Muscle Test for muscle strength, BRS, Fugl–Meyer Assessment of the Lower Extremities, Berg Balance Scale, Functional Ambulation Category, modified Rankin scale, and Short-Form Health Survey version 2. As a muscle strength measurement test, the Manual Muscle Test is evaluated on a scale of 0–5 according to strength against gravity and resistance. In this study, the Manual Muscle Test of the hip flexor, hip abductor, knee extensor, and ankle dorsiflexor will be measured. Manual Muscle Test has good external and internal efficacy and is not dependent on examiner bias [31]. The BRS is a classification method that models the motor recovery process after stroke-induced hemiplegia on a 6-point ordinal scale. The Brunnstrom approach focuses on the unique patterns associated with stroke recovery, including spasticity development, synergistic patterns, and voluntary movements. The BRS has high inter-rater reliability (0.74–0.98) [32]. The Fugl–Meyer Assessment of the Lower Extremities investigates hip, knee, and ankle movements, and hierarchical recovery is recorded based on Brunnstrom stages of recovery from reflex to synergistic and non-synergistic movements. The Fugl–Meyer Assessment of the Lower Extremities motor domain uses a 3-point ordinal scale: 0, unable to perform; 1, partial performance; and 2, complete performance. Possible scores range from 0 to 34. The intra- and inter-rater reliabilities are excellent in early stroke patients [33]. The Berg Balance Scale was developed to objectively measure balance and fall risk in community-dwelling older adults using a three-step survey of 32 health professionals. The Berg Balance Scale examines 14 movements of daily life on a 5-point ordinal scale from 0–4, and the total score ranges from 0–56. The Berg Balance Scale is widely used to assess stroke patients, and its test-retest reliability and internal consistency are excellent [34]. The Functional Ambulation Category is a 6-point rating scale that assesses the amount of human support required when walking (with or without a personal assistive device). A score of 0 indicates a non-functional ambulator, and a score of 1–3 indicates a dependent ambulator. A score of 1 indicates the need for continuous manual contact, 2 indicate intermittent or continuous light touch, and 3 indicates supervision or verbal cues. Scores of 4–5 indicate an independent ambulator, with a score of 4 indicating independent ambulators on horizontal surfaces only and a score of 5 indicating independent ambulators on any surface, including stairs. There is good inter-rater reliability among examiners in post-stroke patients [35]. The modified Rankin scale is a widely used tool to measure global disability after stroke. The scale classifies disability from 0 (no symptoms) to 5 (severe disability). Scoring is performed by an evaluator based on patients’ functional dependence. The intra-rater reliability is excellent [36]. The Rivermead Motor Assessment consists of three sections, and sections of gross function and leg and trunk are evaluated in this study. The gross function section consists of 13 items and primarily assesses mobility from sitting to running and gait, and the leg and trunk section describes individual movements of the trunk (e.g., rolling to the affected side) and leg (e.g., ankle dorsiflexion with the leg extended while lying down). The intra-class correlation coefficients of the Rivermead Motor Assessment is between 0.88 and 0.95 [37]. The Short-Form Health Survey version 2 is a well-studied self-reported measure of functional health. The items include physical functioning, physical role limitation, pain, general medical health, vitality, social functioning, emotional role limitation, mental health, physical component scale, and mental component scale. There is good internal consistency of >0.7 for all the subscales of the questionnaire [38]. Among the assessments for the baseline status and primary and secondary outcomes, the official Korean version of the Fugl–Meyer Assessment, Berg Balance Scale, Short-Form Health Survey 36 version 2, and the Hospital Anxiety and Depression Scale will be used in this study [39–42]. The assessors who are proficient in English will conduct the English version of the assessments, including the Pittsburgh Rehabilitation Participation Scale, Rivermead Motor Assessment, Manual muscle test, Brunnstrom recovery stage, modified Rankin scale, and Functional Ambulation Category. The Short-Form Healthy Surgery 36 version 2 and the Hospital Anxiety and Depression Scale are self-administered questionnaires, and all other evaluations are clinician-administered assessments. All primary and secondary outcomes will be assessed at baseline, and at 3 weeks and 12 weeks. Assessments will be performed over two days to manage fatigue and reduce potential bias in stroke patients. The Fugl–Meyer Assessment, Berg Balance Scale, Manual muscle test, and Short-Form Health Survey 36 version 2 will be conducted on the first day, and the Rivermead Motor Assessment, Brunnstrom Recovery Stage, modified Rankin Scale, and Functional Ambulation Category will be conducted on the second day. Participants will be instructed and familiarized before the actual assessments to help them understand the evaluation processes and improve compliance. Regular breaks will be provided during assessment sessions to prevent fatigue and maintain the participants’ attention.

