In this study, the PRPS is implemented as the primary outcome to assess patient engagement in in-bed self-exercises based on the EMG activities, addressing the absence of direct supervision by physical therapists. It categorizes patient participation into three types of exercise sessions, including participating, effortful, and successful sessions, which are defined by the number and percentage of contractions of target muscles and EMG amplitude of target muscles during contractions in this study. This approach allows physical therapists to evaluate the degree of patient participation in in-bed self-exercises quantitatively and to aid in planning the dose and intensity of future sessions without direct supervision. Using PRPS measurements based on EMG activities can be beneficial to assess patient participation in various forms of self-rehabilitation where therapist involvement is minimal.

The multicenter setting of this study may lead to potential inconsistencies between sites with respect to outcome assessments and exercises instructions. To mitigate this issue, careful monitoring and standardization of assessment techniques along with exercises instructions will be necessary. The research group will coordinate training sessions to implement proper assessment techniques and standardization at both study sites and hold regular meetings to maintain adherence to standard operating procedures.

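### The primary outcome has two incompatible definitions, and the EMG-based one, as described, can be scored only in the intervention arm over weeks 1-3

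*Protocol article*

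**What the plan says.** Section 2.5.1 names the PRPS as primary outcome and introduces it as a clinician-administered scale from 1 to 6. Later in that section, apart from two self-completed questionnaires, "all other evaluations are clinician-administered assessments", and assessors are to use the English PRPS.

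The same section also gives a different scoring rule: "In the PRPS, there are three types of exercise sessions to be newly defined as follows". A session is participating, effortful or successful according to the number of target-muscle contractions and their amplitude, with thresholds of 20% and 50% of maximal voluntary contraction. Then: "The six categories of PRPS using the concept of participating, effortful, and successful sessions are defined as follows". Section 3 explains the purpose: "the PRPS is implemented as the primary outcome to assess patient engagement in in-bed self-exercises based on the EMG activities".

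Sections 2.1 and 2.4.2 describe EMG self-exercise as the addition given to the intervention arm. Controls receive conventional rehabilitation alone. Section 2.5.1 limits the self-exercise period to 3 weeks and treats week 12 as follow-up.

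Three other statements rely on this outcome:
- Section 1 hypothesises that "there will be a statistically significant difference in Pittsburgh Rehabilitation Participation Scales among subacute stroke patients" between the two treatments.
- Section 2.5.1 says: "All primary and secondary outcomes will be assessed at baseline, and at 3 weeks and 12 weeks".
- Section 2.8 analyses outcomes with a linear mixed model containing time (three levels), group and their interaction.

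**The concern.** The two definitions measure different things. One is a rater's judgement of how a patient takes part in a therapy session. The other is a compliance score computed from sensor data on unsupervised exercise. Only the first can exist in both arms.

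The hypothesis, visit schedule and model all assume a score for every patient at every time point. Under the EMG rule, no text says how to score a control, or anyone at baseline or week 12. The analyst would have to improvise, and each choice gives a different primary result: no comparison at all, a comparison of two different instruments, or an arbitrary value assigned to controls. The secondary outcomes built on the same sessions (the three session types, contraction amplitude and exercise duration) inherit the problem.

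**Working it through.** **Inputs**
- Self-exercise in the intervention arm (section 2.4.2): at least 2 sessions a day, 5 days a week, 3 weeks.
- Self-exercise in controls (sections 2.1 and 2.4): none described, and no EMG recording or maximal-contraction reference is described for them.
- Time points and model terms: sections 2.5.1 and 2.8.
- Sample size (section 2.1): 20, raised for 15% loss. 20 / 0.85 = 23.5, rounded up to 24, as stated. This figure is not in dispute, and the protocol gives no effect size or power for the PRPS.

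**Step 1: the denominator.** Intervention patients have at least 2 × 5 × 3 = 30 prescribed sessions. Controls have 0, so their percentage of participating sessions is 0/0, which is undefined rather than 0%.

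**Step 2: which cells can be scored by the EMG rule.**

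| Arm | Baseline | Week 3 | Week 12 |
|---|---|---|---|
| Control | no sessions | 0/0 | no sessions |
| Intervention | not yet started | scorable from at least 30 sessions | period ended 12 − 3 = 9 weeks earlier |

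One of 2 × 3 = 6 cells can be filled.

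**Step 3: what the model can estimate.** Write the fixed part as

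mean = b0 + b1·(week 3) + b2·(week 12) + b3·group + b4·group×(week 3) + b5·group×(week 12).

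With all six cells, the design has rank 6. The single scorable cell contributes the row (1, 1, 0, 1, 1, 0), so the rank is 1. A contrast is estimable only if it is a multiple of that row.
- Group difference at week 3, b3 + b4, row (0, 0, 0, 1, 1, 0): not estimable.
- Group difference at week 12, b3 + b5, row (0, 0, 0, 1, 0, 1): not estimable.
- Interaction terms b4 and b5: not estimable.
- Intervention mean at week 3, b0 + b1 + b3 + b4: estimable, and the only such quantity up to scaling.

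The missing-data methods in section 2.8 do not help. Control values would be undefined rather than missing, and with no control observed there is nothing to impute from.

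**Step 4: the other definition.** Both arms receive conventional therapy twice a day, five days a week (section 2.4.1), so 2 × 5 × 3 = 30 sessions over weeks 1-3. A clinician-rated PRPS on those sessions could be scored in both arms. No section says that this is the primary endpoint, which sessions it rates, or over what period.

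**The case against.** The best defence is that the primary outcome is the ordinary clinician-rated PRPS. Section 2.5.1 describes it so and has assessors conduct it. Both arms have therapy to be rated, and the Fig 2 legend lists "the number and percentage of completed conventional physiotherapy sessions" among the outcomes. On that reading the hypothesis can be tested. It is also fair that no sentence states that controls wear no sensors, that Figs 2, 9 and 10 are not shown, and that the two-day assessment list in section 2.5.1 omits the PRPS, so it may have its own timing in a figure.

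This defence shows that a workable definition was available, not that it was chosen. Section 2.5.1 gives a full scoring rule only for the EMG version, and section 3 says that this version is the primary outcome. The conventional-session counts are not linked to the PRPS anywhere. The contradiction therefore stands, and the claim that the outcome cannot be tested must be limited to the EMG rule.

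A reader might infer something stronger: that every control scores none, so the trial succeeds by construction. The text does not support that. The category is tied to 0% participating sessions, or to declining or doing nothing within a session, whereas a control has no such session. Scoring controls as none would be an added convention. Nor would success follow whatever the true participation, since an intervention patient with no participating session also scores none.

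**Conclusion.** The plan is wrong as written on its primary outcome. It holds two incompatible definitions, and the one it spells out fills one of six arm-by-time cells. For that score the between-group hypothesis and all group and interaction contrasts are not estimable; only the intervention arm's own result over weeks 1-3 is. This rests on the arm descriptions being complete, so that controls have no EMG-recorded self-exercise, and on the unseen figures not supplying another rule.

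If controls were nevertheless scored none, the comparison would mainly reflect which arm was given the device. As an illustration only, with a test that is not the planned one: with 10 per arm (20 / 2) and all controls at none, five intervention patients above none give a two-sided Fisher p of 2 × C(10,5) / C(20,5) = 504 / 15504 = 0.033, although half the arm did nothing. That shows why the convention should not be adopted; it does not describe what the protocol plans.

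**What to change.** 1. Give the EMG-based score its own name. Report it for the intervention arm only, over weeks 1-3, as the feasibility estimate with a 95% confidence interval, together with the session counts, contraction amplitude and exercise duration. Remove all of these from the baseline and 12-week schedule and from the time-by-group model.
2. If a between-group comparison of participation is wanted, use the original clinician-rated PRPS on conventional sessions that both arms receive in weeks 1-3. State which sessions are rated and by whom, and keep the raters blinded.
3. Restate the hypothesis in section 1 to match, and align sections 2.5.1, 2.8 and 3.

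Steps 1 and 3 cost only wording. Step 2 adds rating time. Rating every conventional session would mean up to 30 × 24 = 720 ratings, and would fit poorly with section 2.3, where two blinded therapists, one from each institution, assess the outcomes. A stated subset is enough; one session per patient per week, for example, is 3 × 24 = 72 ratings. No extra patients are needed.

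### The six EMG-based PRPS categories that define the primary outcome leave two regions without a score and overlap in two places

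*Protocol article*

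**What the plan says.** Section 2.5.1 makes the PRPS the primary outcome and redefines its six levels through three session types: participating (more than one contraction of the target muscles), effortful (amplitude above 20% of maximal voluntary isometric contraction) and successful (above 50%). The levels are:

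- *None*: "i) none, 0% of participating sessions".
- *Poor*: "ii) poor, <50% of participating sessions".
- *Fair* and *good*: "iii) fair, ≥50% of participating sessions and <50% of effortful sessions; (iv) good, ≥90% of participating sessions, ≥50% and <90% of effortful sessions".
- *Very good*: "v) very good, ≥90% of participating sessions, ≥90% of effortful sessions, and ≥90% of successful sessions".
- *Excellent*: the same three cut-offs as *very good*, plus active involvement in planning future sessions.

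Section 2.4.2 gives the amount of self-exercise in two places. Participants are told to complete "at least two 30-minute sessions per day, 5 days a week, for a duration of 3 weeks". The prescribing principles recommend "2 types of self-exercises per session, 2–3 sessions per day, 3–5 sets per session, and 5–10 repetitions per set", to be settled by the physiatrist or physical therapist. The article does not say which number of sessions the percentages are taken over.

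**The concern.** A categorical primary outcome needs a rule that gives each patient one level and no more. Here *fair* stops at 50% effortful, while *good* starts only at 90% participating, so the space between them is empty. *Good* also stops at 90% effortful, while *very good* asks in addition for 90% successful, which leaves a second empty space.

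An assessor who meets a result in either space must leave the PRPS blank or improvise a level. The affected results are defined by participation and effort, which is what the outcome measures. If they were left blank, the missing-data methods of section 2.8 would be applied to patients whose sessions were in fact recorded. With 12 patients planned per group, a few such cases would count.

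**Working it through.** The plan gives no figure on this point to reproduce. The check applies the six definitions literally to every possible result.

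**Inputs.** P, E and S are the numbers of participating, effortful and successful sessions, with S ≤ E ≤ P ≤ N. Section 2.4.2 gives 2 × 5 × 3 = 30 sessions at two per day and 3 × 5 × 3 = 45 at three. *Very good* and *excellent* are pooled, since they differ only by involvement in planning. The base is an assumption: first N for all three percentages, then an alternative.

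**Number of possible results.** (N+3)(N+2)(N+1)/6, which is 33 × 32 × 31/6 = 5,456 for N = 30 and 48 × 47 × 46/6 = 17,296 for N = 45.

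**Region A: 50% ≤ P < 90%, E ≥ 50%.** For N = 30, P runs from 15 to 26, E from 15 to P, and S takes E + 1 values. Summing (E + 1)(27 − E) over E = 15 to 26 gives 1,534. For N = 45, P runs from 23 to 40, and summing (E + 1)(41 − E) over E = 23 to 40 gives 5,073.

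**Region B: P ≥ 90%, E ≥ 90%, S < 90%.** For N = 30, there are 10 pairs (P, E) with 27 ≤ E ≤ P ≤ 30 and 27 values of S (0 to 26): 270. For N = 45, there are 15 pairs and 41 values of S: 615.

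**Unscored share.**

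| Base | Region A | Region B | Total | Share |
|---|---|---|---|---|
| N = 30 | 1,534 | 270 | 1,804 of 5,456 | 33.1% |
| N = 45 | 5,073 | 615 | 5,688 of 17,296 | 32.9% |

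If E and S are instead taken over attended sessions, the unscored share is 2,574 of 5,456 (47.2%) for N = 30 and 8,508 of 17,296 (49.2%) for N = 45. The gaps do not depend on the choice of base.

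**Examples, N = 30.**

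- Every attended session successful: 1 to 14 attended is *poor*, 15 to 26 has no category, and 27 to 30 is *very good* or *excellent*. This holds on either base.
- 30 attended, 26 effortful (86.7%), 0 successful: *good*. With 27 effortful (90%) and 0 successful: no category. More effort loses the score, again on either base.
- 30 attended, 30 effortful, 26 successful (86.7%): no category.

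**Overlaps.** P = 0 satisfies P = 0% and also P < 50%, so it is both *none* and *poor*. A patient who meets *excellent* also meets every condition of *very good*.

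**Why the base needs naming.** 28 attended with 14 effortful is 28/30 = 93.3% participating. Effortful is 14/30 = 46.7% over 30 sessions (*fair*), but 14/28 = 50% over attended sessions (*good*).

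**The case against.** The shares above weight every possible result equally. A reader might infer that a third of patients will go unscored, or that many compliant patients will. The document gives no distribution of adherence or EMG amplitude, so neither can be said. Among results with at least 90% participating, the unscored share is lower: 270 of 1,802 (15.0%) at N = 30 and 615 of 4,955 (12.4%) at N = 45.

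A reader might also infer that the denominator changes with each patient's prescription. If it were prescribed sessions, 30 fully successful sessions would be 30/30 = 100% at two per day but 30/45 = 66.7% at three. No section says so, however. The two statements of amount are compatible, since two to three per day satisfies a minimum of two, and an article may leave the base to a fuller document. What stands is that the article does not name the base and that 30 to 45 sessions are allowed.

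The PRPS is described as clinician-administered, so an assessor might place a gap case by judgement. That would make the score hard to reproduce rather than missing, so informative missingness is a possible consequence and not an established one. Fig 9 is not shown and might be clearer, but the text presents a full set of six definitions. The session counts and percentages are also secondary outcomes, so the raw components survive and a complete rule can be set before analysis. This limits the harm but does not close the gaps.

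**Conclusion.** The point holds for the definitions as written. The categories leave two regions empty, overlap at zero participation and between the top two levels, and can withdraw a score when effort rises. At a common base of 30 or 45 sessions, about 33% of possible results are unscored, and 47% to 49% if effort and success are taken over attended sessions. How many patients this affects cannot be computed. Because the outcome is primary and the rule cannot be applied to results such as 24 of 30 sessions all done with effort, it should be repaired before any PRPS is scored. The unstated base and the mismatch at 50% amplitude are smaller points to settle at the same time.

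**What to change.** Score from the top down: assign the highest category whose lower bounds are all met, and delete the upper caps.

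- *Excellent* and *very good*: as written, checked in that order.
- *Good*: at least 90% participating and at least 50% effortful.
- *Fair*: at least 50% participating.
- *Poor*: above 0% participating.
- *None*: 0% participating.

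Every category cut-off stays, and every result that already had one category keeps it. Region A goes to *fair* and region B to *good*. At N = 30 the counts become *none* 1, *poor* 679, *fair* 1,920 + 1,534 = 3,454, *good* 1,032 + 270 = 1,302 and the top two levels 20, which sum to 5,456. The downside is that some high-adherence results, such as 26 of 30 sessions all successful, fall in *fair*. The rule scores every set of three percentages; it does not settle how those percentages arise where no self-exercise is recorded.

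Name one base for all three percentages before analysis. A base of 30 capped at 100% should not be used: a patient with 27 successful sessions out of 45 would score 27/30 = 90% successful, although 27/45 = 60% were.

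Reconcile the amplitude wording: section 2.4.2 sets the exercise target at 50% or above, while section 2.5.1 counts a session as successful only above 50%.

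The cost is wording in section 2.5.1 and Fig 9 and a line of scoring code. No new data are needed.
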